#### Audio recording

All face-to-face and telephone contacts will be recorded via dictaphone for quality control. Audio recordings will be stored securely with password protection. Written informed consent from participants will be sought before obtaining audio recordings.

#### Primary outcome measures

There are two primary outcomes: changes from baseline to post-intervention in the ISI [53], the gold standard for assessing insomnia symptoms, and self-reported sleep efficiency (SE_s_)_._ SE_s_ will be obtained from the daily sleep diary based on the consensus sleep diary [54]. SE_s_ is calculated using the ratio of self-reported total sleep time divided by the total time spent in bed for sleep. Outcomes will be measured by observing the change in participants’ average SE_s_ between the first week and the last week of the intervention. SE_s_ is commonly used as an indicator of progress in insomnia treatment as high sleep efficiency scores indicate consolidated sleep [55–57].

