## Method

### Study design

This is a randomised, two-group, parallel, non-blinded, controlled, single-centre, superiority trial. One group will receive combined CBT plus BLT (CBT+). The other group will receive treatment as usual enhanced with a relaxation audio programme serving as an active control (TAU+). All participants will be involved in the trial for the 6-week duration. Measures will be taken at baseline, at the mid-point of the intervention (3 weeks) and post-treatment (6 weeks). A follow-up assessment will occur at 3 months to evaluate any sustained effects of the intervention on primary and secondary outcomes. This trial and protocol adhere to SPIRIT [48] and TIDieR [49] recommendations.

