### Sample size and power

Based on previous studies of CBT for insomnia and sleep in people with cancer and BLT [69–74] we expect a moderate to large effect size for both primary outcomes. Given that our combined CBT+ targets multiple and different mechanisms of change, we expect larger effects than shown in previous studies utilising only CBT or BLT. Specifically, we expect a standardised mean difference of *d* = 0.70, corresponding to a medium-to-large between-group effect at the post-treatment assessment.

Power analyses based on an independent samples *t* test showed that a total of 70 women will provide >80% power to detect a standardised mean difference of 0.70 at post-treatment, assuming α = 0.05 and equal variance between groups. Power analyses are not readily available for latent growth models (LGMs) and require complex simulations. Therefore, we chose power analysis based off a *t* test as a conservative estimate as, due to randomisation, no baseline differences between conditions are expected so the difference in the slopes from LGMs between treatment and control will be based on post-treatment mean differences but should have lower variability because of removing variability due to individual differences at baseline. Thus, we anticipate the LGMs will have more power than a *t* test based on post-treatment scores and that our power estimates are conservative, although final power will depend on the difference, variability, and correlations in data over time, which are unknown. We will continue recruitment until we reach 70 completers. Progress to date is shown in Fig. 1.

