Treatment effects will be evaluated by creating a dummy code (0 = TAU+, 1 = CBT+). This dummy code will be entered as a predictor of the intercept, slope 1 and slope 2. However, treatment factors will be constrained to 0 for the intercept, to implement so-called constrained longitudinal data analysis, which studies show provides a more accurate estimate of treatment effects from randomised controlled trials with repeated measures [78, 79].

The primary trial results will be the effect of treatment on slope 1 (i.e. from week 0 to week 6). This interaction directly tests whether the change in primary outcomes over time is different in the control and intervention arm. Effect sizes of the group difference at each time point also will be calculated.

A similar process will be followed for sleep efficiency; however, a continuous time, linear model will be estimated using a mixed effects model in Mplus because up to 42 days of sleep efficiency are collected. A piecewise model is not needed as sleep diary data are not collected at follow-up due to burden. Sleep efficiency may not follow a normal distribution. If the assumption of normality is violated, significance tests and confidence intervals will be based on non-parametric bootstrapping.

#### Aim 2

Aim 2 is to test the efficacy of CBT+ versus TAU+ for psychological outcomes. Aim 2 will be tested identically to aim 1, but using psychological outcomes in place of the sleep and fatigue outcomes.

#### Aim 3

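### Two primary outcomes have no stated success rule, so the single alpha of 0.05 and power above 80% cannot be tied to a defined efficacy claim

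*Protocol article*

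**What the plan says.** Under Primary outcome measures the protocol article states: "There are two primary outcomes: changes from baseline to post-intervention in the ISI" and, alongside it, self-reported sleep efficiency from the daily diary.

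Under Sample size and power it says "we expect a moderate to large effect size for both primary outcomes". It then gives one calculation, for an independent-samples t test with d = 0.70 after treatment: "a total of 70 women will provide >80% power". The level used in that calculation is given by the words "assuming α = 0.05 and equal variance between groups". The target is 70 completers.

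Under Statistical analyses, Aim 1, the ISI is analysed in a piecewise latent growth model: "The primary trial results will be the effect of treatment on slope 1", meaning weeks 0 to 6. Sleep efficiency gets its own mixed model by a similar process.

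None of these sections ranks the two outcomes, divides alpha, adjusts for multiplicity, or says whether one or both must be significant. The Aim 1 hypothesis refers only to measures of sleep disturbance in general. The 0.05 in the power paragraph is the only significance level in the document.

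**The concern.** With two primary outcomes, the error rate and power of the trial depend on what counts as success. The protocol gives an alpha and a power for one test and leaves open how two tests combine into an efficacy conclusion.

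As written, nothing stops either outcome from carrying the claim at 0.05, which raises the chance of a false positive. If both outcomes are needed instead, the quoted power is too high for the planned number of completers. A split result is plausible: one outcome is a questionnaire and the other a diary ratio, and the section on secondary outcomes itself accepts that not every dimension of sleep may change. The statisticians are not blinded and both primary outcomes are unblinded self-reports. Without a rule fixed in advance, the headline result could be chosen after the data are seen.

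**Working it through.** **Inputs.** From Sample size and power: 70 women in total, d = 0.70, alpha 0.05, equal variances, with a moderate to large effect expected on both outcomes. From Trial status: 101 randomised. Assumed because not stated: two-sided tests, 1:1 allocation (35 per arm), d = 0.70 on each outcome, and a correlation r between the two test statistics, shown from 0 to 0.9. The 0.05 is carried from the power paragraph to the efficacy tests.

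**1. The plan's own figure.** Noncentrality = 0.70 × √(35 × 35 / 70) = 2.928, with 68 degrees of freedom and critical t = 1.995. Power is 82.3% (83.4% by normal approximation). The stated figure reproduces for one outcome.

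**2. Either outcome suffices, each at 0.05.** At r = 0 the type I error is 1 − 0.95² = 9.75%. For correlated tests it is 1 − P(|Z₁| < 1.96 and |Z₂| < 1.96) under a bivariate normal.

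**3. Both outcomes required, each at 0.05.** Power is Φ₂(z, z; r), the bivariate normal probability, with z = Φ⁻¹(0.823). At r = 0 this is 0.823² = 67.7%.

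**4. Fixed sequence, ISI first.** The error rate is held at 5%, because sleep efficiency is tested only after ISI succeeds. Power is 82.3% for ISI; power for both is as in step 3.

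**5. Holm.** Each test at 0.025 has power 73.7%. At least one outcome succeeds with probability 2 × 0.7365 − Φ₂ (both at 0.025); at r = 0 this is 1 − (1 − 0.7365)² = 93.1%. A named outcome succeeds if its p < 0.025, or if its p < 0.05 and the other p < 0.025; at r = 0 this is 0.7365 + (0.8230 − 0.7365) × 0.7365 = 80.0%.

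| r | Either-outcome type I error | Power, both at 0.05 | Holm, at least one | Holm, a named outcome |
|---|---|---|---|---|
| 0 | 9.75% | 67.7% | 93.1% | 80.0% |
| 0.3 | 9.5% | 70.0% | 89.6% | 79.4% |
| 0.5 | 9.1% | 71.9% | 87.0% | 78.9% |
| 0.7 | 8.3% | 74.3% | 83.9% | 78.4% |
| 0.9 | 7.0% | 77.7% | 79.5% | 77.5% |

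Power for both passes 80% only at near-perfect correlation (79.0% at r = 0.95, 80.8% at r = 0.99).

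**6. All 101 randomised women giving data (50 and 51), an upper bound.** One outcome at 0.05: 93.6%. Both, at r = 0: 0.936² = 87.6%, and higher with positive correlation. One outcome at 0.025: 89.1%.

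**The case against.** - **A valid rule may fit the stated figures.** A reader might infer that alpha 0.05 with power above 80% fits no valid two-outcome rule. That is wrong. A fixed sequence with ISI first gives 82.3% for ISI at a controlled 5%, and Holm gives about 80% to 93% for at least one outcome. The sample size is compatible with sound rules. What is missing is a statement of which one applies.
- **The test level is inferred.** The 0.05 appears only in the power paragraph; Statistical analyses sets no level for the efficacy tests. This stands as a caveat, although no other level is offered.
- **The trial may not be underpowered.** A reader might infer that it is. The shortfall for both outcomes applies to the 70-completer t-test basis. The protocol expects its growth models to do better, while saying the variability and correlations are unknown. With 101 women randomised, the gap may be covered. This largely answers the power concern in practice, but not the error rate.
- **Near-doubling is the ceiling.** The 9.75% is the value at zero correlation. Two self-reported sleep measures in the same women are probably positively correlated, so the excess is likely smaller. It is still 7.0% at r = 0.9.
- **The rule may be in a document not shown.** The article says the full protocol and analysis code will be posted separately, and multiplicity rules often sit in an analysis plan. That would supply the rule. But this article itself names two primary outcomes and justifies the sample size with one undivided alpha, so its power statement would still need to say which claim it supports.

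**Conclusion.** The point holds as a should-fix. Two primary outcomes, separate models and a single-test power statement leave the efficacy claim undefined. If either outcome suffices at 0.05, the type I error is about 7.0% to 9.75% rather than 5%, and this does not shrink with sample size. If both must succeed, power is about 68% to 78% at the planned 70 completers, against the stated figure above 80%.

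These results rest on two-sided tests, 1:1 allocation, d = 0.70 on both outcomes, bivariate normal test statistics with r between 0 and 0.9, and the 0.05 in the power paragraph being the level used for each outcome. They do not show that the achieved trial lacks power, nor that its sample size is incompatible with every valid rule.

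**What to change.** State one error-controlling rule, dated and fixed before analysis and without sight of results by arm. Recruitment has closed, but this protocol version predates the expected end of follow-up in January 2020. Two workable choices:

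- **Fixed sequence:** test ISI at two-sided 0.05 and treat sleep efficiency as confirmatory only if ISI is significant. The protocol's description of the ISI as the reference measure for insomnia symptoms supports this order but does not oblige it; the investigators should confirm the priority.
- **Holm across the two outcomes:** neither needs to be ranked first.

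Then restate Sample size and power for the chosen rule at 70 completers. For the fixed sequence: 82% for ISI and about 68% to 78% for both. For Holm: about 80% to 93% for at least one outcome and about 77.5% to 80% for each. Say that the correlation is assumed, and report the 101 randomised separately.

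The cost is a sentence and a more qualified power statement. Under the fixed sequence, sleep efficiency cannot support a stand-alone confirmatory claim if ISI misses. Under Holm, power for each outcome is slightly below the single-test 82%.

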#### Secondary outcome measures

Secondary outcomes will include additional dimensions of sleep behaviours assessed via self-reported sleep diaries and actigraphy, and symptoms of fatigue, depression and anxiety. Sleep-onset latency, wake after sleep onset and total sleep time will be derived from the sleep diaries and the ActiGraph. The ActiGraph wGT3X-BT records continuous activity information using a three-axis accelerometer along with ambient light. Using the activity data, the wGT3X-BT provides estimates for sleep timing (bed time and rise time), sleep duration (time in bed and total sleep time), and sleep quality (sleep efficiency, sleep-onset latency, wake after sleep onset). Actigraphy data scoring will follow standard protocol, integrating estimates from the automated scoring algorithm along with ambient light, and sleep diary reports of bed and rise time. Actigraphy sleep assessments are time and date stamped so that they can be matched with the self-report sleep diary measures. In sleep studies it is common to evaluate the impact of interventions on multiple behavioural dimensions of sleep as not all dimensions may change. Furthermore, it is helpful to supplement self-reported sleep with an objective measure (actigraphy). Evidence suggests that, often, there is only modest agreement between sleep diary and actigraphy, suggesting that these two measures capture unique information and are not redundant [58].

The Patient-Reported Outcomes Measurement Information System (PROMIS) scales will be used to assess other secondary outcomes including sleep-related impairment and sleep disturbance [59], fatigue [60], and mental health measures of depression and anxiety [61].

### Sample size and power

Based on previous studies of CBT for insomnia and sleep in people with cancer and BLT [69–74] we expect a moderate to large effect size for both primary outcomes. Given that our combined CBT+ targets multiple and different mechanisms of change, we expect larger effects than shown in previous studies utilising only CBT or BLT. Specifically, we expect a standardised mean difference of *d* = 0.70, corresponding to a medium-to-large between-group effect at the post-treatment assessment.

Power analyses based on an independent samples *t* test showed that a total of 70 women will provide >80% power to detect a standardised mean difference of 0.70 at post-treatment, assuming α = 0.05 and equal variance between groups. Power analyses are not readily available for latent growth models (LGMs) and require complex simulations. Therefore, we chose power analysis based off a *t* test as a conservative estimate as, due to randomisation, no baseline differences between conditions are expected so the difference in the slopes from LGMs between treatment and control will be based on post-treatment mean differences but should have lower variability because of removing variability due to individual differences at baseline. Thus, we anticipate the LGMs will have more power than a *t* test based on post-treatment scores and that our power estimates are conservative, although final power will depend on the difference, variability, and correlations in data over time, which are unknown. We will continue recruitment until we reach 70 completers. Progress to date is shown in Fig. 1.

**Fig. 1 Fig1:**
[figure not shown]
CONSORT participant flow chart of recruitment. CBT+ combined cognitive behavioural therapy and bright light therapy, TAU+ treatment as usual plus relaxation audios

### Statistical analyses

Primary analyses will be conducted on an intention-to-treat basis. Thus, results for all randomised women will be analysed in the group to which they were assigned, regardless of protocol violations. The only exception to this will occur if participants withhold or withdraw consent to use their data in the analysis. Statistical analyses will be conducted in R (data management, graphs, preliminary analyses) and MPlus using MplusAutomation [75]. As a preliminary step, data will be assessed for outliers and skew and, where appropriate, transformed or winsorised. Prior to primary analyses, we will produce a thorough descriptive profile of the sample, characterising both the dropout and missing data. There are no interim analyses planned. Statisticians will not be blinded.

#### Baseline comparisons

Participant characteristics at baseline will be presented by treatment group, and statistical tests will be conducted to verify that randomisation was successful. Discrete variables will be summarised by frequencies and percentages, and baseline group differences tested using chi-square tests. Continuous variables will be summarised using mean (standard deviation) or median (interquartile range) and baseline group differences, tested using independent *t* tests or Wilcoxon signed-rank tests for variables that evidence non-normal distributions. If there are significant differences in any participant characteristics at baseline, the variable(s) will be included as covariates in the final analyses.

#### Aim 1

Aim 1 is to test the efficacy of CBT+ compared to TAU+ for improving symptoms of sleep disturbance. Aim 1 will be tested using LGMs. LGMs will be estimated with an intercept and two linear slopes, representing a piecewise model. Slope 1 will have loadings constrained to 0, 0.5, 1.0 and 1.0 for weeks 0, 3, 6 and 12, respectively, capturing the linear change from baseline (week 0) to post-intervention (week 6). Slope 2 will have loadings constrained to 0, 0, 0 and 1.0 for weeks 0, 3, 6 and 12, respectively, allowing a different slope from post-intervention (week 6) to follow-up (week 12) compared to from baseline (week 0) to post-intervention (week 6). The means and variances of the intercept and slope factors will be freely estimated (corresponding to random effects in linear mixed models) and the intercept and slope covariances will be estimated. The residual variance will be constrained to equality across time and residuals assumed uncorrelated, corresponding to an independent, homogenous residual structure. Intercepts of indicators will be constrained to 0 to allow estimation of the latent random intercept mean.

There are two stratification factors: screening ISI (≤7, ≥8) and cancer stage (≤2, ≥3). These factors will be crossed, creating four groups: early-stage, low ISI; advanced-stage, low ISI; early-stage, high ISI; and advanced-stage, high ISI. Dummy codes will be created for each strata, with early-stage, low ISI treated as the reference group. These dummy codes will be included as covariates to adjust for their effect on the random intercept following recommendations that stratification factors be adjusted for in analyses of randomised controlled trials [76, 77].

Treatment effects will be evaluated by creating a dummy code (0 = TAU+, 1 = CBT+). This dummy code will be entered as a predictor of the intercept, slope 1 and slope 2. However, treatment factors will be constrained to 0 for the intercept, to implement so-called constrained longitudinal data analysis, which studies show provides a more accurate estimate of treatment effects from randomised controlled trials with repeated measures [78, 79].

The primary trial results will be the effect of treatment on slope 1 (i.e. from week 0 to week 6). This interaction directly tests whether the change in primary outcomes over time is different in the control and intervention arm. Effect sizes of the group difference at each time point also will be calculated.

A similar process will be followed for sleep efficiency; however, a continuous time, linear model will be estimated using a mixed effects model in Mplus because up to 42 days of sleep efficiency are collected. A piecewise model is not needed as sleep diary data are not collected at follow-up due to burden. Sleep efficiency may not follow a normal distribution. If the assumption of normality is violated, significance tests and confidence intervals will be based on non-parametric bootstrapping.

#### Aim 2

Aim 2 is to test the efficacy of CBT+ versus TAU+ for psychological outcomes. Aim 2 will be tested identically to aim 1, but using psychological outcomes in place of the sleep and fatigue outcomes.

#### Aim 3

Aim 3 is to explore potential mechanisms of CBT+ and moderators of the intervention efficacy. Mechanisms (i.e. pre-sleep arousal, beliefs and attitudes about sleep, vulnerability to insomnia under stress and intrusive thoughts before bed) will be tested using mediation conducted in path analyses. Specifically, we will examine the effect of condition on change in mechanisms (for example, pre-sleep arousal) from baseline to treatment mid-point, and test whether the change in mechanisms from baseline to treatment mid-point accounts for the condition effects on change in outcomes (for example, ISI) from baseline to post-treatment and follow-up. Statistical mediation will be determined by evaluating the indirect effects, calculated as the product of the paths from condition to change in mechanisms and from change in mechanisms to change in outcomes. Bootstrapping will be used to estimate the confidence interval for indirect effects and their statistical significance. Given the modest sample size, analyses will be conducted for each mechanism and outcome individually.

Treatment moderators (i.e. pain, chronotype, perceived credibility and expectations of the intervention, and adherence to the intervention protocol) will be evaluated by modifying the primary linear mixed effects analyses from aims 1 and 2 to include a condition × moderator interaction, along with all lower order effects predicting slope 1 and slope 2 of the piecewise model. Individual moderators will be tested in separate models.

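### Extra covariates are picked by significance tests on baseline characteristics, so selection ignores prognostic value and the primary model is not fixed in advance

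*Protocol article*

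**What the plan says.** In the protocol article, Statistical analyses, Baseline comparisons, the arms are to be compared on participant characteristics with chi-square, t or Wilcoxon tests. The stated purpose is that "statistical tests will be conducted to verify that randomisation was successful". The consequence is mandatory: "If there are significant differences in any participant characteristics at baseline, the variable(s) will be included as covariates in the final analyses". Significance is the only criterion given for entry; prognostic value is not mentioned.

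Three other statements bear on this:

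- Aim 1 already specifies covariates. Screening ISI (≤7, ≥8) is crossed with cancer stage (≤2, ≥3), and of the resulting codes it says: "These dummy codes will be included as covariates to adjust for their effect on the random intercept".
- Aim 1 also constrains the arms to be equal at baseline: "treatment factors will be constrained to 0 for the intercept, to implement so-called constrained longitudinal data analysis".
- Sample size and power gives the premise behind that constraint: "due to randomisation, no baseline differences between conditions are expected".

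The opening of Statistical analyses adds: "Statisticians will not be blinded".

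**The concern.** If allocation was properly generated and concealed, as the Randomisation section describes, every significant baseline difference is a chance event. A p-value for such a difference measures the size of the imbalance relative to sampling error. It carries no information on whether the variable predicts insomnia symptoms or sleep efficiency. The rule can therefore add irrelevant variables that happen to differ and omit strong predictors whose imbalance falls short of significance.

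Two things are at stake. The primary model is not known until the baseline tests have been run, so the treatment effect on slope 1 depends on a pre-test. And any precision to be had from a further prognostic covariate is mostly forgone, because that covariate enters only when it happens to be imbalanced.

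The rule also sits awkwardly with the plan's own reasoning: balance is expected in the power section and built into the Aim 1 model, yet it is tested, and acted upon, in Baseline comparisons.

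**Working it through.** **Inputs.** From Sample size and power: 70 women in total, d = 0.70, "assuming α = 0.05 and equal variance between groups". From Trial status: 101 women randomised. Assumed, because the document does not state them: two-sided tests, 1:1 allocation, a 5% threshold for the baseline tests, the number k of characteristics tested, and the correlation rho between a covariate and the outcome.

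**1. The plan's own figure.** With 35 per arm the noncentrality is 0.70 × √(35/2) = 2.93. The normal approximation gives Φ(2.93 − 1.96) = 83.4%, and the exact noncentral t gives 82.3%. The stated power above 80% reproduces.

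**2. How often the rule acts by chance.** For k independent tests at 5%, P(at least one significant) = 1 − 0.95^k, and the expected number selected is 0.05k.

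| k (assumed) | P(at least one enters) | Expected number |
|---|---|---|
| 10 | 40% | 0.5 |
| 20 | 64% | 1.0 |
| 25 | 72% | 1.25 |

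Positive correlation among characteristics would lower the middle column.

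**3. How large an imbalance must be to be selected.** The threshold in SD units is t(0.975; 2n − 2) × √(2/n). With 35 per arm it is about 0.48 SD; with 50 per arm, close to the 101 randomised, about 0.40 SD. A smaller imbalance in a strong predictor stays unadjusted.

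**4. Consequence for the test.** 20,000 simulated trials per setting, 35 per arm, with one baseline covariate and a single post-treatment outcome. Three strategies were compared: never adjust, always adjust, and adjust only if the baseline test has p < 0.05.

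| rho | Type I error, always | Type I error, rule | Power at d = 0.70, always | Power, rule |
|---|---|---|---|---|
| 0.3 | 5.0% | 4.9% | 85.1% | 82.4% |
| 0.5 | 4.9% | 4.2% | 91.0% | 82.9% |
| 0.7 | 5.2% | 3.8% | 98.0% | 84.2% |

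Never adjusting gave about 82% power throughout. The covariate was selected in about 5% of trials whether rho was 0 or 0.7, so selection was unrelated to prognostic value. The simulation standard error near 5% is √(0.05 × 0.95/20,000) = 0.15 percentage points. The 4.9% is thus indistinguishable from nominal, while 4.2% and 3.8% are below it.

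**5. Limit of step 4.** The simulated model contains neither a baseline outcome nor strata. The planned ISI model contains both, so the relevant rho is what a further covariate explains beyond them. The power gaps at rho 0.5 and 0.7 show the direction of the effect, not the loss to be expected in this trial.

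**The case against.** The best defence is that the rule is written down in advance and is triggered by baseline data, not by outcomes. The ISI model already uses the week-0 value as its first measurement and always adjusts for the strata, so only additional covariates depend on the rule. A candidate list may stand in the full protocol. A baseline test can also flag faulty implementation of randomisation. All of this stands, and it confines the point to the additional covariates. It does not rescue significance as the selection criterion, which the article states outright.

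A reader might infer several stronger criticisms that the document does not support:

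- **That the rule contradicts the equal-baseline constraint.** It does not. The plan says that "treatment factors will be constrained to 0 for the intercept"; entering another baseline variable is compatible with that, just as the stratum dummies are.
- **That week-0 ISI will be entered as a covariate.** The protocol nowhere says so, and stratification on ISI makes a large imbalance less likely. The wording merely fails to exclude it.
- **That the rule inflates false positives.** The simulation points the other way.
- **That unblinded statisticians will choose the model from the results.** The absence of blinding is a reason to fix the model early; the stated trigger is still a baseline comparison.

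**Conclusion.** The point holds as one of pre-specification and efficiency. The stated rule selects chance imbalances irrespective of prognosis and leaves the primary model unsettled until baseline data are tested. The chance that it adds at least one variable is 40% to 72% for an assumed 10 to 25 independent tests at 5%. That range measures how often the model would change, not bias in the treatment effect.

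The expected harm is a mildly conservative and less precise test, limited to covariates beyond the baseline outcome and strata. The amount cannot be fixed from the document: it depends on the unstated number of tests and on how much a further covariate would explain. The validity of the primary test is not threatened. The rule should nonetheless be changed, because the wrong criterion is stated explicitly and the remedy is cheap.

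**What to change.** Delete the baseline significance tests and the conditional-covariate rule, and present baseline characteristics by arm descriptively. Keep the primary model with the stratification dummies already specified. Add a short list of prognostic covariates only if it is fixed on prior clinical grounds before any outcome data are examined, and say how each enters the intercept and slopes. State that the outcome's own week-0 value is not a candidate, since it is already in the growth model. Report any adjustment for observed imbalance as a labelled sensitivity analysis.

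Timing favours the strata-only model. Recruitment closed in October 2019 with 101 women randomised, and the statisticians are unblinded, so a list drawn up now could be influenced by the baseline data.

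The cost is a wording amendment, communicated to the ethics committee and participants as the protocol requires for modifications; no new data or participants are needed. The trade-off is that a chance imbalance is then handled in a sensitivity analysis and not in the primary model.
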